#### Statistical methods

The study groups will be compared at baseline regarding known determinants of cardiovascular care and its improvement. These include patient factors [27,28] (*e.g.*, age, multi-morbidity, ethnicity at practice level) and practice characteristics [22,29] (*e.g.*, availability of nurses, delegation of medical tasks to assistance, practice size). Only factors emerging from previous research are considered to avoid overcorrection in the primary analysis. A logistic regression model will be constructed for each outcome to analyze these outcomes in relation to group (intervention, control) and measurement moment (baseline, follow-up). Identified differences between the groups at baseline will be included in this analysis. Random coefficients will be included to allow for the clustering of data within practices. Each of the secondary outcomes (clinical and organizational indicators) will also be analyzed in this way. Finally, if an internally consistent scale can be constructed (reflected by high reliability coefficients of the combined score), we will develop an aggregated measure of outcome, and use this in a similar random coefficients linear regression analysis.

To identify the effectiveness of this program on attainment of practice-defined goals and its perceived unintended consequences, the second key objective, a descriptive analysis will be performed aimed at determining what proportion of self-defined goals for improvement was achieved by the practices and straightforward listing of the GP views on unintended consequences of the practice accreditation program.

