#### Randomization

General practices will be the unit of randomization. A computer list of random numbers will be generated by an independent statistician and then used to randomly allocate practices to equally sized intervention group or control group. This will be done in a randomized block design in blocks of four practices in order of enrolment. We assume that improvement activities in the control group will not influence cardiovascular care.

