#### Sample size

In the practices in the practice accreditation program up to 2006 (n = 139), the following median values at practice level were found on indicators referring to patients with CVD: 53% for acceptable blood pressure levels; 36% for acceptable cholesterol levels; and 38% for use of anticoagulents (unpublished data at IQ healthcare, 2005 and 2006). These data suggest that the current scores on the primary outcomes are in the range of 35% to 55%, which imply that substantial improvement is possible in many practices. The proposed study has been powered to detect a difference of 10% (from 55% to 65%), not yet taking control for baseline values into account because of uncertainty regarding the correlation between baseline and follow-up measures.

We expected that the accreditation and improvement program will have an effect of 5% to 10% absolute change, which is the median value of effect sizes in a comprehensive review of 235 studies on quality improvement [14]. Other assumptions were a power = 0.80, alpha = 0.05, and ICC = 0.05. Given the sample of 30 patients per practice per indicator, we aimed to include 31 practices in each group. Allowing for dropout, we aim to include 35 practices in each group (n = 70 practices in total). This number is feasible, given the recruitment rate for the accreditation in 2006.

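### The power of 0.80 is for a follow-up-only comparison, while the planned two-moment model leaves its treatment term unnamed; a common-baseline or baseline-adjusted contrast would guarantee at least that power at no cost

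*Protocol article*

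**What the plan says.** The Sample size section of the protocol article powers a rise from 55% to 65%. It states: "Other assumptions were a power = 0.80, alpha = 0.05, and ICC = 0.05". It continues: "Given the sample of 30 patients per practice per indicator, we aimed to include 31 practices in each group". Recruitment is then raised to 35 per arm for dropout. The calculation is described as "not yet taking control for baseline values into account because of uncertainty regarding the correlation between baseline and follow-up measures".

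The Statistical methods section describes one logistic model per outcome, "to analyze these outcomes in relation to group (intervention, control) and measurement moment (baseline, follow-up"). On the random part it says: "Random coefficients will be included to allow for the clustering of data within practices". It does not say whether the treatment effect is the group-by-moment interaction, a follow-up difference with a shared baseline, or a follow-up difference adjusted for the baseline outcome. The baseline differences that are to enter the model appear to be determinants of care, such as patient factors and practice characteristics, and not the outcome itself.

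Under Measurement procedures, 40 records per practice are audited at baseline. Under Intervention group, practices are randomised after the baseline data are collected. Under Ethical approval and informed consent, the follow-up patients come from 100 invited per practice. Whether they are the same patients as at baseline is not stated.

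**The concern.** The abstract attaches the power to the intention-to-treat analysis, but the figure was computed for a simpler comparison than the model described. Leaving baseline out of a power calculation is conservative if baseline is later used as an adjustment. It is not conservative if baseline is subtracted. A group-by-moment interaction subtracts the baseline difference between arms, and with it brings in the sampling error of the baseline percentages. If practice effects are only moderately stable between the two moments, that error outweighs what is gained.

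At stake is precision. Depending on which term is reported, the same data could give clearly less or clearly more power than the article states.

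**Working it through.** **Inputs.** From Sample size: 0.55 versus 0.65, power 0.80, alpha 0.05 (sidedness not stated), ICC 0.05, 30 patients per practice, 31 practices per arm (35 recruited). From Measurement procedures: 40 baseline records. I show 30 baseline records as well, because the 30 per indicator in Sample size might apply at both moments.

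**Assumed, because the article gives no value.** r is the correlation of practice effects between baseline and follow-up, shown from 0 to 1. Different patients are taken at the two moments.

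**Step 1: reproduce the stated figure.** Two proportions, two-sided 0.05, power 0.80: 376 per arm. Design effect 1 + 29 × 0.05 = 2.45. Then 376 × 2.45 / 30 = 30.7, so 31. (A one-sided test gives 24.2 and a continuity correction 32.3, so neither matches.) The figure therefore reproduces as a comparison at follow-up alone.

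**Step 2: variances.** In units of p(1−p), a practice percentage based on m records has variance V = 0.05 + 0.95/m.

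- Follow-up, m = 30: V_f = 0.0817
- Baseline, m = 40: V_b = 0.0738; m = 30: V_b = 0.0817

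The three contrasts have these variances:

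- Follow-up only: V_f
- Interaction (difference in differences): V_f + V_b − 2r(0.05)
- Common baseline or baseline-adjusted: V_f(1 − R²), with R = 0.05r / √(V_f V_b)

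The third is the smallest variance obtainable by subtracting any multiple of the baseline. Follow-up only uses multiple 0 and the interaction uses multiple 1, so neither can beat it.

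**Step 3: power.** Power = Φ(0.10/SE − 1.96), with SE = √(2 × 0.2375 × V / 31) and 0.2375 the mean of 0.55 × 0.45 and 0.65 × 0.35.

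Example at r = 0.5 with 40 baseline records:

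- Interaction: V = 0.0817 + 0.0738 − 0.05 = 0.1054, SE = 0.0402, power 0.70.
- Common baseline: R² = 0.025² / (0.0817 × 0.0738) = 0.104, V = 0.0732, SE = 0.0335, power 0.85.

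| 31 practices per arm, 30 follow-up records | r = 0 | r = 0.5 | r = 0.8 | r = 1 |
|---|---|---|---|---|
| Follow-up only | 0.81 | 0.81 | 0.81 | 0.81 |
| Interaction, 30 baseline records | 0.52 | 0.67 | 0.80 | 0.89 |
| Interaction, 40 baseline records | 0.54 | 0.70 | 0.84 | 0.93 |
| Common baseline, 30 baseline records | 0.81 | 0.84 | 0.90 | 0.95 |
| Common baseline, 40 baseline records | 0.81 | 0.85 | 0.91 | 0.96 |

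**Step 4: break-even.** The interaction loses to follow-up only when V_b > 2r(0.05), that is, when r < V_b/0.10. This is r below about 0.82 with 30 baseline records, or 0.74 with 40.

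**Step 5: no dropout.** With all 35 practices per arm kept and 40 baseline records, follow-up only has 0.85. At r = 0.5 the interaction has 0.75 and the common-baseline contrast 0.89.

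**The case against.** Four points can be made for the plan.

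- **Detail left to the analysis plan.** A condensed article need not spell out a model's parameterisation. The Sample size section speaks of controlling for baseline values, which fits baseline adjustment, and random coefficients may already include a practice-by-moment effect. This stands in part: the article does not commit to the weaker contrast. It does, however, state both a model and a power figure, and nothing in it ties the two together.
- **The omission is disclosed.** The Sample size section says that baseline is left out, and why. This stands. The disclosure does not add that one natural use of baseline can lower power.
- **Patient overlap.** If the same patients were measured twice, the loss shrinks. For illustration, take full overlap, 30 records at each moment, r = 0.5 and a within-patient correlation of 0.5. The interaction variance is then 2 × (0.025 + 0.0158) = 0.0817, equal to follow-up only. This stands, and so the loss is conditional.
- **The interaction is a valid analysis,** and at high r it beats follow-up only. This stands too.

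A reader might go further and infer that the model has only main effects of group and moment, so that the group term averages over both moments and dilutes the effect. Nothing in the article says that such a pooled term is the test. A reader might also take the r = 0.5 figures as limits, with 0.67 as the lowest power of the interaction and 0.84 as the least for a common baseline. They hold only at that assumed r with 30 records at each moment. Nor do the documents support calling the sample size wrong: it reproduces.

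**Conclusion.** The point holds as a moderate one about precision. The stated 0.80 belongs to a follow-up-only comparison, and the article does not name the treatment term of its two-moment model. If that term is the unconstrained interaction, power with 40 baseline records lies between 0.54 and 0.93 and is below follow-up only when r is under about 0.74. A common-baseline or baseline-adjusted contrast gives 0.81 to 0.96 and is not below follow-up only at any r.

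This rests on assumed values of r, on different patients at the two moments, on 30 usable follow-up records per practice, and on a normal approximation on the risk-difference scale in place of the logistic model. The small cost of estimating the baseline adjustment is ignored. No bias is shown, and whether power is actually lost depends on a term and a correlation that the article does not give.

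**What to change.** In Statistical methods, name the primary treatment effect as the difference between groups at follow-up. Either constrain the arms to be equal at baseline, which is justified because baseline data are collected before randomisation, or adjust for the practice's own baseline percentage. For the constrained two-moment model, state a fixed effect of moment, a random practice effect and a random practice-by-moment effect. Say whether the same patients may appear at both moments.

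In Sample size, state that 0.80 is the power of the follow-up-only comparison and is the floor for this model.

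The cost is wording in two sections. No extra practices, records or measurements are needed. The Discussion says that no data had been cleaned or analysed before submission, so the choice can be fixed before any result is known.

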#### Other measures

1. Exposure to other quality improvement activities: Both study groups report on their exposure to relevant professional education and practice improvement activities (*e.g.*, training for practice nurses). This will be measured in semi-structured telephone interviews.

2. Potential confounders: At follow up, potential confounders will be measured. These include patient characteristics, particularly patient age, gender and multi-morbidity. Furthermore, data on practice characteristics will be collected. These include practice size, physician workload, volume of assistance in the practice, delegation of medical tasks to assistants, and involvement of practice nurses in chronic care. These practice characteristics have shown to be associated with better chronic disease management in Dutch primary care practices [22].

3. Patient reported outcomes: At follow up, patients receive questionnaires that include items on demographic characteristics, labor activities and healthcare use. Furthermore the EQ-5D (five items and VAS scale) will be added to measure health outcome [23]. To measure chronic care delivery, the Patient Assessment of Chronic Illness Care (PACIC) will be used [24]. Questionnaires for physical exercise (RAPA, nine items) [25], and the Treatment Self-Regulation Questionnaire (TSRQ) [26] to measure the motivation for being physically active will be included.

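### Covariates enter the outcome models only where the randomised arms are seen to differ at baseline, so chance imbalance decides the adjusted model

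*Protocol article*

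**What the plan says.** The rule is in the protocol article under Statistical methods and has three steps.

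- Comparison: "The study groups will be compared at baseline regarding known determinants of cardiovascular care and its improvement". The examples are three patient factors ("age, multi-morbidity, ethnicity at practice level") and three practice factors ("availability of nurses, delegation of medical tasks to assistance, practice size").
- Limit on candidates: "Only factors emerging from previous research are considered to avoid overcorrection in the primary analysis".
- Entry into the model: "Identified differences between the groups at baseline will be included in this analysis".

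The model for each outcome is a logistic regression on group and measurement moment, with random coefficients for practice. Those terms are fixed. The secondary indicators are handled the same way. No test, threshold or size of difference is given.

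Two statements under Other measures bear on this. On the practice factors: "These practice characteristics have shown to be associated with better chronic disease management in Dutch primary care practices". On timing: "At follow up, potential confounders will be measured".

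Under Intervention group, practices are randomised after baseline data have been collected. Under Randomization, allocation follows a computer list in blocks of four.

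**The concern.** Since allocation follows baseline data collection and is random, a baseline difference between the arms can only be chance. The reason to adjust in a randomised trial is that a covariate predicts the outcome. Whether it happens to be unbalanced is a separate matter. The article identifies factors it believes to be predictive and then admits only those that chance has made unequal.

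Two things are at stake. First, the model behind the primary odds ratios is settled only once the allocated arms have been compared, by a judgement the article does not define. In a logistic model the conditional odds ratio depends on which covariates are in it, so the quantity estimated changes with that judgement. This applies mainly to patient-level factors, because the random practice terms already condition on practice. Second, a strong predictor that is balanced is left out, and its precision is lost.

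**Working it through.** **Inputs from the article.** Under Sample size: 55% versus 65%, power 0.80, alpha 0.05, ICC 0.05, 30 patients per practice, 31 practices per group before dropout. Under Statistical methods: six example candidates.

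**The plan's own figure.** With a two-sided alpha and the pooled-variance formula,
n = [1.96·√(2·0.60·0.40) + 0.8416·√(0.55·0.45 + 0.65·0.35)]² / 0.10² = (1.358 + 0.580)² / 0.01, which rounds up to 376 per arm.
The design effect is 1 + 29·0.05 = 2.45. Then 376·2.45 = 921.2, and 921.2/30 = 30.7, so 31 practices. The stated number reproduces, and the covariate rule does not affect it.

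**How often chance alone would change the model.** Assume k independent candidates and a 5% screen; neither assumption is in the article. P(at least one flagged) = 1 − 0.95^k.

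- k = 3: 14.3%
- k = 6 (the named examples): 26.5%
- k = 12: 46.0%
- k = 6 with a 10% screen: 1 − 0.90^6 = 46.9%

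At a 5% screen any one candidate, however predictive, stays out in about 95% of trials.

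**What the rule costs in precision.** Both simulations use 31 practices per arm and one practice-level covariate screened at p < 0.05. The strength of the covariate (R²) is assumed.

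1. *Follow-up comparison only, baseline outcome ignored* (10,000 runs; R² is the share of the variance of practice means). Power under the rule versus a pre-specified covariate:
   - R² 0.10: 0.79 versus 0.82
   - R² 0.25: 0.79 versus 0.88
   - R² 0.50: 0.81 versus 0.97
2. *Baseline outcome used* (4,000 runs, linear approximation, 30 patients per practice, ICC 0.05; R² is the share of true between-practice variance). Power under the rule versus a pre-specified covariate:
   - R² 0.10: 0.93 versus 0.93
   - R² 0.25: 0.93 versus 0.94
   - R² 0.50: 0.93 versus 0.95
   - Practice-level correlation over time of 0.8: largest gap 0.87 versus 0.90

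The second setting is closer to the planned model, which includes the baseline measurement. A practice characteristic that is constant over time largely cancels from the contrast between baseline and follow-up. Neither simulation covers patient case-mix.

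**Type I error under the rule.** It was 0.045, 0.045 and 0.035 in the first setting (R² 0.10, 0.25, 0.50) and 0.046 to 0.053 in the second, so there is no inflation.

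**The case against.** The case for leaving the rule alone has four parts.

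- *The candidates are restricted.* Only factors from previous research are eligible, so chance chooses among plausible predictors. This stands as a real safeguard. It narrows the pool but leaves the choice within it to chance.
- *The baseline outcome is already in the analysis.* Measurement moment is a model term, so each practice's prior performance is used. This stands, and it removes most of the precision argument for practice-level factors.
- *The covariate list and the threshold are details for a full protocol or SAP.* This also stands, and their absence is not the point. The article does state the principle of entry by observed imbalance, and that principle is what is wrong.
- *Inference remains valid.* A reader might infer that selecting covariates this way inflates type I error or makes the standard errors anti-conservative. The calculations do not support that: the error rate stays near 5% or falls below it.

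Two further readings go too far. Pooling the confounders under Other measures with those under Statistical methods gives eight or nine candidates and a chance of 34% to 37% (1 − 0.95^8, 1 − 0.95^9), or about one trial in three. But the first list is of confounders measured at follow-up, the second is given only as examples, and practice size, nurse availability and delegation are unlikely to be independent. The large power loss (0.81 versus 0.97) belongs to a follow-up-only comparison, which is not the planned analysis.

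**Conclusion.** The concern holds in a limited form. The article fixes a rule under which chance imbalance, judged by no stated criterion, decides the covariates in every outcome model, and balanced predictors are dropped. The consequences are a data-dependent model, a conditional odds ratio whose meaning is not settled in advance, and some lost precision.

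The 26.5% for the six named factors, and the range of 14% to 46%, illustrate how easily chance could change the model. They rest on independence and a 5% screen, neither of which the article states. The power loss for a practice-level covariate is probably small once the baseline outcome is used: zero to three percentage points in the settings tried. For patient case-mix it has not been quantified. The rule should be replaced, but it does not threaten the validity of the primary test.

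**What to change.** 1. Delete the sentence that admits covariates by baseline difference. Before analysis, name a short list of prognostic covariates drawn from the factors already identified, for example patient age, sex, multi-morbidity and practice size. Include them in every outcome model whatever the observed balance.
2. Keep the baseline comparison of the arms as description only, and label any further adjustment a sensitivity analysis.
3. Use the baseline outcome once: either through the planned model of group by measurement moment, or as a covariate in a follow-up-only model. Adding it as a covariate to a model that already holds the baseline observations as outcomes would use it twice.
4. Restrict the list to factors that allocation cannot affect, or for which pre-randomisation values exist. Other measures places confounder measurement at follow-up, by which time nurse involvement, delegation or recorded multi-morbidity could have changed.

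The cost is a few sentences of text. The Discussion says no data had been cleaned or analysed at submission, so at that point the change could be made without sight of results. The article does not show that no new data are needed. Practice characteristics without a baseline value must be recorded at baseline or left out. If the model keeps the baseline observations, patient covariates are needed for those patients too.

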#### Economic analysis

The economic analysis, the third key objective, aims to determine the efficiency of the program in the observed period regarding the primary outcomes. The economic evaluation also investigates the relationship between costs, performance indicators, and accreditation. The economic evaluation provides incremental cost-effectiveness ratios: incremental cost per percentage patients gained with systolic blood pressure below 140 mmHg; incremental cost per percentage patients gained with LDL cholesterol <2.5 mmol/l; incremental cost per percentage patient gained with aspirin, an alternative anti-platelet therapy or an anti-coagulant.

For the economic analysis, costs analyses will be based on the competing health production processes respectively, including and excluding resources attributed to accreditation. Specific unit-costs include, for example medical care (contacts in primary care practice, tests, treatments, etc.) and improvement related costs (accreditation tariff, time for audit, planning and implementing improvement, exposure to other relevant quality improvement, etc.). Units of resources are monetary valued on the basis of prevailing Dutch guidelines [30] or national CVZ tariffs. The analysis aims to provide incremental cost-effectiveness ratios (ICERs). The ICERs will be computed, and uncertainty will be determined using the bootstrap method to account for skewness in the underlying parameter distributions. Uncertainty will be presented in a Bayesian fashion using cost-effectiveness acceptability curves (CEAC’s) that are able to evaluate efficiency by using different thresholds for the ICER (varying the willingness to pay for a percentage patients gained for each of the primary outcomes). Uncertainty in deterministic parameters will be examined with sensitivity analysis based on the range of extremes.

#### Process evaluation

The process evaluation, the fourth key objective, aims to explore what factors and mechanisms are associated with change (or absence of change) of performance on CVRM indicators. Semi-structured telephone interviews will be held with primary care physician or the quality coordinator of the practice after data collection for follow-up measurement is concluded. Topics of this interview are: practice characteristics; feedback reports; composing improvement plans; and reasons to participate in and experiences with the practice accreditation program. We want to explore if specific elements of the practice accreditation program are the cause of change in CVRM. All interviews will be conducted by the same person and will be audio-recorded. Interviews will be transcribed verbatim. Two researchers will independently review the transcripts. Data analysis will be done according to the framework approach [31]. Topics in the interviews will be used as coding frame. Software package Atlas ti. will be applied to analyze qualitative data. The primary analysis of the interview data aims to identify determinants of (change of) practice as perceived by participants.

